### Concealment mechanism {16b}

The allocation sequence will be concealed by using sequentially numbered, opaque sealed envelopes.

### Implementation {16c}

The sealed envelopes will be opened and concealed again in the operating room prior to the operation by the anesthetic nurse and the OR nurse. The nurses will not participate in the treatment of the patient outside the operating room. The enrollment will be performed by the surgeons at the pre-surgery visit at the outpatient clinic.

## Assignment of interventions: blinding

### Who will be blinded {17a}

Trial participants, surgeons, and the anesthesiologist will be blinded to interventions. All participants will be administered both LTAP and local wound injections (analgesic and placebo) as described earlier. The injectable analgesics will be prepared by the OR nurse and the anesthetic nurse, who also open the sealed envelopes. The needles, the syringes, and the injectable amounts are the same in both groups.

### Procedure for unblinding if needed {17b}

In case of a severe allergic reaction after levobupivacaine infiltration, unblinding will be performed in order to reveal the exact dosage of levobupivacaine administered.

## Data collection and management

### Plans for assessment and collection of outcomes {18a}

Data will be collected prospectively on an electronic SPSS-database designed for this study. Validated questionnaires (NRS and EHP-30) will be used at the baseline and for collecting outcome data concerning postoperative pain and 6-month follow-up. These are filled in on paper questionnaires by the patients and transferred into SPSS database by two authors who double-check each other’s work.

### Plans to promote participant retention and complete follow-up {18b}

Any trial participant lost to follow-up will be contacted in order to complete the 6-month follow-up.

### Data management {19}

All data will be handled with utmost care and confidentiality. Data will be stored electronically with passwords and any manual data will be stored behind locked doors in the department. Data entry is possible only for the authoring investigators.

### Confidentiality {27}

The unique personal ID codes given by the Finnish government at birth or immigration will be used to link data originated at different phases of the study. For analyses, only pseudonymized data will be handled, using ID codes generated for this study. A separate key file connecting the unique personal ID codes and the study ID codes will be created and stored in hospital server where only primary investigators (AT, SK) have access.

### Plans for collection, laboratory evaluation, and storage of biological specimens for genetic or molecular analysis in this trial/future use {33}

Not applicable. No biological specimens will be collected.

## Statistical methods

### Statistical methods for primary and secondary outcomes {20a}

Statistical analyses will be performed on an intention-to-treat basis using IBM SPSS software by the study statistician who does not participate in patient care or data collection. Continuous variables will be described as mean with standard deviation (SD) or as median with 25th–75th percentiles and categorical variables as numbers and percentage of proportions. Comparison between the study groups will be conducted using the Student’s *t*-test or Welch test for continuous variables, Mann-Whitney *U* test for variables measured at ordinal scale, and the chi-square or Fisher’s test for categorical variables. Furthermore, continuous variables with measurements both pre- and postoperatively will be analyzed using linear regression model with preoperative measurement as an adjusting factor. The statistical significance limit is set at two-sided *p*-value < 0.05.

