## Introduction

### Background and rationale {6a}

Endometriosis is a chronic disease affecting about 10% of women during their fertile years. Patients often suffer from chronic pelvic pain that decreases markedly their quality of life. Conservative hormonal medication, being the primary treatment option, is often insufficient due to persisting pain, contraindications, or side-effects such as irregular bleeding. Hence, there is also need for surgical treatment of peritoneal endometriosis [1]. Clinical observations have shown that patients with endometriosis tend to suffer from more severe postoperative pain after pelvic surgery than other patients [2]. This may be due to hypersensitization of sensory pelvic nerves, which is caused by the inflammatory nature of endometriosis. Dysmenorrhea, which is the leading symptom of endometriosis, is a prognostic factor for the severity of postoperative pain [3]. The use of epidural or local wound analgesia after endometriosis surgery has been common practice. However, local wound analgesia is often insufficient for endometriosis patients, who tend to suffer from more severe postoperative pain [2]. Epidural analgesia carries a risk of potentially harmful complications and may also prohibit enhanced recovery after surgery (ERAS) and prolong time to discharge. In addition, postoperative opioid consumption also predisposes to complications such as nausea, vomiting, and respiratory depression.

Dorsally inserted transversus abdominis plane block (TAP) has been used as a part of multimodal analgesia in abdominal surgery since the beginning of twenty-first century [4]. TAP blocks the sensory nerves of the abdominal wall unilaterally between the costal margin and the inguinal ligament (T6–L1), and it provides analgesia to the parietal peritoneum, muscles, and abdominal skin accordingly [5]. When inserted in a blind fashion, it carries a risk of visceral injury. To avoid complications, ultrasound-guided transversus abdominis plane block technique (UTAP) was adopted by anesthesiologists. Both methods have been shown to serve as an effective postoperative analgesia reducing postoperative opioid consumption and opioid-related side effects after open and laparoscopic abdominal surgery [6].

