### Intervention description {11a}

#### Outpatient clinic

After giving informed consent, study participants will fill in preoperative validated questionnaires regarding pain (Numeric Rating Scale, NRS) and endometriosis-related health (Endometriosis Health Profile, EHP-30).

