### Outcomes {12}

Primary outcome is the overall 24 h postoperative opioid consumption compared between the study groups. The amount of oxycodone administered via the PCA-pump and possible rescue analgesics (oxycodone administered in addition to the PCA-pump) will be converted to morphine equivalents.

As secondary outcomes, the following will be measured:
Postoperative pain using NRS scaled from 0 to 10 (0 meaning no pain and 10 meaning “worst imaginable pain”). The maximum experienced pain will be recorded at the recovery room. Additional NRS will be recorded at the ward every six hours up to 24 h (if the patient is discharged before 24 h, they are requested to fill in the NRS at home).Factors related to ERAS (nausea, vomiting, peroral intake, mobilization, complications, time of discharge, readmission to hospital) will serve as other outcomes and will be documented and analyzed accordingly.A 6-month postoperative follow-up will be conducted using NRS pain inquiry and EHP-30 questionnaire being sent to participants.

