### Participant timeline {13}

### Sample size {14}

Sample size was calculated based on the assumption that LTAP would decrease the postoperative opioid consumption by 50%, which was thought to be a clinically relevant difference. The calculation was based on previous literature showing a 15.4 mg ± 9.2 postoperative opioid consumption after local wound analgesia [15]. With 80% power and 0.05 alpha error, the sample size of 46 (23 + 23) was obtained to detect a decrease of 7.7 mg in opioid consumption from 15.4 mg in the control group to 7.7 mg in the intervention group, assuming a standard deviation of 9.2 mg. Sample size was calculated according to Chow et al. [16], and the calculation was performed with statistical program R.

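### The adjustment rule leaves the primary outcome unadjusted although preoperative pain is recorded; adding it as one covariate is a cheap efficiency gain, not the repair of an error

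*Protocol article*

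**What the plan says.** The Outcomes section {12} defines the endpoint: "Primary outcome is the overall 24 h postoperative opioid consumption compared between the study groups". It is expressed in morphine equivalents and has no preoperative counterpart. Patients on continuous opioids before surgery are excluded under Eligibility criteria {10}.

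The statistical methods section {20a} assigns Student's t-test or the Welch test to continuous variables. It then adds one rule for adjustment: "continuous variables with measurements both pre- and postoperatively will be analyzed using linear regression model with preoperative measurement as an adjusting factor". That rule covers pain scores and EHP-30 but cannot reach opioid consumption. The primary comparison is therefore unadjusted by the plan's own wording.

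A baseline pain score is nevertheless planned. Under Outpatient clinic in {11a}, "study participants will fill in preoperative validated questionnaires regarding pain (Numeric Rating Scale, NRS) and endometriosis-related health". The Background {6a} says: "Dysmenorrhea, which is the leading symptom of endometriosis, is a prognostic factor for the severity of postoperative pain". The Discussion repeats this for severe dysmenorrhea. Sequence generation {16a} specifies simple randomization and mentions no stratification.

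**The concern.** The one outcome on which the trial's conclusion rests is the one that the adjustment rule leaves out. The protocol argues that these patients' pain history matters for pain after surgery, and PCA use is driven by the patient, so a link between preoperative pain and opioid use is plausible. If it exists, a baseline covariate would narrow the confidence interval without new data.

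The trial has little power to spare, with 46 patients and a calculation that only just reaches its target. Simple randomization also does nothing to limit chance differences in baseline pain between the arms. At stake is a few points of power and some protection of the estimate against such differences.

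**Working it through.** **Inputs from the documents.** Sample size {14} gives the size and its error rates: "With 80% power and 0.05 alpha error, the sample size of 46 (23 + 23) was obtained". The same section sets the target difference at 7.7 mg, half of a control mean of 15.4 mg, and takes the SD as 9.2 mg. Under {20a}, tests are two-sided at the 0.05 level.

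**Input by assumption.** r, the correlation of preoperative NRS with 24 h opioid consumption, is not in the documents. The range 0 to 0.5 is shown.

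**Step 1, the plan's own figure.** Normal approximation, two-sided: n per arm = 2 × (1.960 + 0.842)² × (9.2/7.7)² = 22.4, rounded up to 23, so 46 in total. The stated size reproduces, with power 81.0% by this approximation.

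**Step 2, unadjusted t-test at 23 per arm.** Noncentrality = 7.7 / (9.2 × √(2/23)) = 2.838 on 44 df. Power = 79.3%.

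**Step 3, adjusted for one covariate.** The residual SD becomes 9.2 × √(1 − r²). One degree of freedom is spent, leaving 43. Chance imbalance in the covariate raises the variance by an expected factor of 1 + 1/(46 − 4) = 43/42. Noncentrality = 7.7 / (9.2 × √(1 − r²) × √(43/42) × √(2/23)).

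| r (assumed) | Noncentrality | Power | Change from 79.3% |
|---|---|---|---|
| 0 | 2.805 | 78.3% | −1.0 |
| 0.2 | 2.863 | 79.9% | +0.6 |
| 0.3 | 2.941 | 82.0% | +2.7 |
| 0.4 | 3.061 | 84.9% | +5.6 |
| 0.5 | 3.239 | 88.6% | +9.3 |

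Without the 43/42 factor, power at r = 0.3, 0.4 and 0.5 would read 82.9%, 85.7% and 89.3%, which is slightly too favourable.

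**Step 4, break-even.** Apart from the lost degree of freedom, adjustment pays once (1 − r²) × 43/42 < 1. That means r² > 1/43 = 0.023, or r above about 0.15.

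**Step 5, chance imbalance.** The SE of the between-arm difference in a standardized covariate is √(2/23) = 0.295. A difference of at least 0.3 SD therefore has probability of about 0.31. At r = 0.4, a difference of that size moves the unadjusted estimate by 0.4 × 0.3 × 9.2 = 1.1 mg, which is 14% of 7.7 mg.

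**Step 6, robust standard errors.** Simulated with 46 patients, simple randomization, equal variances and r = 0.3, the NRS-adjusted model with HC3 errors has power 79.6%, against about 78.5% for the t-test. Both lie below the fixed 23 + 23 figures, partly because arm sizes vary under simple randomization.

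**The case against.** The strongest reply is that nothing here is wrong. A t or Welch test is valid under randomization, and it is the analysis for which the trial was sized. Its standard error already allows for chance imbalance, so its error rate is not inflated. The quoted adjustment sentence is right for the outcomes it covers. All of this stands, and it limits the point to an improvement.

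A reader might infer that the protocol itself calls preoperative pain prognostic for the primary outcome, so that power is being given away for nothing. The documents do not support this. The predictor they name is dysmenorrhea, and what it predicts is the severity of postoperative pain. They do not say that the baseline NRS measures dysmenorrhea, or that any baseline variable predicts opioid use. With no correlation stated, the gain is conditional: negligible at r = 0.2 and slightly negative at r = 0.

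A reader might also want to add surgeon, since two laparoscopists operate. The documents give no sign that surgeon is prognostic, and the term costs a further degree of freedom. If surgeon explains nothing, power falls to about 81.0%, 84.0% and 87.8% at r = 0.3, 0.4 and 0.5.

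It can also be said that covariates are often left to an analysis plan. That answers a protocol that is silent. This one states a rule, and the rule leaves the primary outcome out.

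**Conclusion.** The point holds as a low-cost efficiency improvement. It is neither an error nor a contradiction. The plan's rule leaves 24 h opioid consumption unadjusted while a plausible covariate is already being collected.

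If preoperative NRS correlates with opioid use at 0.3 to 0.5, power at 23 per arm rises from 79.3% to between 82.0% and 88.6%. The downside is about 1 point of power if the correlation is zero. That trade favours adjustment, but the size of the benefit cannot be established from the documents.

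The figures rest on the assumed r, a common SD of 9.2 mg, equal arms, a linear relation and ordinary standard errors.

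**What to change.** In {20a}, prespecify the primary analysis as a linear regression of 24 h opioid consumption on arm and preoperative NRS, with no other covariate. Say which preoperative NRS value is meant if more than one is recorded. Report the unadjusted Welch comparison as supporting. If robust standard errors are wanted as the counterpart of Welch, name a small-sample type such as HC3 and accept a smaller gain.

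The cost is one sentence and one degree of freedom, with no new data, visits or patients. The change must be made before unblinding, because an adjusted primary analysis chosen afterwards would be post hoc.

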### Interim analyses {21b}

No interim analyses will be performed.

### Methods for additional analyses (e.g., subgroup analyses) {20b}

No preplanned subgroup analyses will be performed.

### Methods in analysis to handle protocol non-adherence and any statistical methods to handle missing data {20c}

Per-protocol analyses will be performed as sensitivity analyses when protocol violations occur. In the case of missing data, a multiple imputation (MI) method will be used. If the results of the MI analysis differ from the original, then both results will be presented. In the case of an arbitrary missing case pattern, the fully conditional specification will be used as an imputation method. In the case of a monotone missing case pattern, the regression imputation will be used.

### Plans to give access to the full protocol, participant level-data, and statistical code {31c}

Health data is sensitive data and cannot be delivered even if pseudonymized. Statistical code and output may be presented if asked.

## Oversight and monitoring

### Composition of the coordinating center and trial steering committee {5d}

Not applicable. This study is a single-center clinical trial with a short follow-up time and low risks for the participating patients.

### Composition of the data monitoring committee, its role and reporting structure {21a}

No data monitoring committee will be needed for this single-center study.

### Adverse event reporting and harms {22}

Possible adverse events and other unintended effects of the trial will be documented on trial data and medical records. All significant adverse events will be listed specifically. Lethal or severe adverse events will be reported to the Finnish Medicines Agency (Fimea) as soon as possible or within 7 days from getting informed of the adverse event.

### Frequency and plans for auditing trial conduct {23}

All suspected severe adverse events and a statement regarding the safety of the trial participants will be reported to Fimea once a year. Any significant novel perceptions of the medicinal product will be reported to Fimea immediately.

### Plans for communicating important protocol amendments to relevant parties (e.g., trial participants, ethical committees) {25}

In case of possible future protocol modifications, The Ethical Committee at Oulu University Hospital as well as Fimea will be informed.

### Dissemination plans {31a}

The trial results will be published in international peer-reviewed journals focusing on the investigatory field in question.

## Discussion

The purpose of this study is to evaluate the efficacy and safety of laparoscopically guided transversus abdominis plane block (LTAP) in comparison to trocar site local analgesia in laparoscopic surgery for suspected or diagnosed superficial endometriosis. Previously, it has been shown that women with chronic pelvic pain or endometriosis have altered pain experience in form of lower pressure-pain threshold and lower maximal pain tolerance than controls, widespread myofascial dysfunction and pain sensitization beyond the pelvic area [17–19]. Additionally, severe dysmenorrhea, a leading symptom of endometriosis, has been noted to predict the severity of postoperative pain after gynecological laparoscopy [3]. Thus, there is a need for effective postoperative pain management regimen with minimal side effects allowing ERAS. So far, knowledge on LTAP in gynecologic surgery is sparse and inconsistent [12–14]. However, data from gastrointestinal surgery, mainly from laparoscopic cholecystectomies, have shown promising results after using LTAP in postoperative analgesia [7, 8, 11]. This study will offer knowledge on whether LTAP is an efficient tool for postoperative pain management for gynecological patients that would carry minimal risks and diminish postoperative opioid consumption as well as support enhanced recovery and discharge.

## Trial status

This is the protocol number one. The recruitment will begin in April 2021 and will be completed by the end of 2022.

## Abbreviations

ASA: Physical status classification system defined by American Society of Anesthesiologists
EHP-30: Endometriosis Health Profile -30
ERAS: Enhanced recovery after surgery
LTAP: Laparoscopically guided transversus abdominis plane block
NRS: Numeric Rating Scale
N/A: Not applicable
PCA: Patient-controlled analgesia pump
PONV: Postoperative nausea and vomiting
TAP: Transversus abdominis plane block
UTAP: Ultrasound-guided transversus abdominis plane block
